### Sample size determination and sampling strategy

Sample sizes for each aim are detailed below. Sampling strategies were informed by our team’s prior unpublished work within the relatively small, close-knit community of OPOs and lung transplant clinicians. Based these experiences, we anticipate response rates exceeding 70%. Sample size estimates account for this expected level of participation.

To evaluate and minimize potential non-response bias, an interim analysis will be conducted after 40% of the survey samples have been enrolled for Aims 1–3. Key demographic and professional characteristics of responders and non-responders will be compared. If systematic differences are observed, targeted oversampling will be employed to ensure representation of participants with characteristics similar to non-responders for the remainder of enrollment.

### Implementation frameworks guiding the study

This study applies two complementary implementation science frameworks to guide the identification of determinants of LUNDON score usage and the development of implementation toolkits to promote adoption:

1)The Capability, Opportunity, Motivation-Behavior (COM-B) model [16,61] posits that behavior is driven by three essential components: capability (knowledge and skills), opportunity (environmental and social factors), and motivation (automatic and reflective processes). This model provides a structured lens for conceptualizing why specific behaviors related to donor management and organ acceptance occur (or fail to occur) in real-world practice.2)The Theoretical Domains Framework (TDF) [62] consolidates multiple behavior change theories into 14 domains to help systematically identify barriers (factors that impede implementation) and facilitators (factors that promote implementation). The framework supports the selection of tailored strategies to address the identified determinants of behavior.

Together, these frameworks will be used to: (a) identify barriers and facilitators of LUNDON score adoption in clinical practice and map the corresponding behavioral domains [Aim 1]; (b) characterize the behavioral and contextual factors influencing OPO-level donor management decisions related to modifiable LUNDON score variables [Aim 2]; and (c) assess how knowledge of a donor’s LUNDON score and the corresponding estimate of recipient survival influences organ acceptance decisions at the lung transplant center level [Aim 3].

### Aim-Specific Protocols and Data Collection

#### Aim 1: Identify determinants (barriers and facilitators) of LUNDON score adoption.

We will conduct a sequential explanatory mixed-methods study consisting of a national survey (quantitative phase, n = 242) followed by semi-structured interviews (qualitative phase, n = 60). Sample size estimates are guided by the concept of “information power”, which indicates that more specialized participant insight allows for smaller sample sizes. Information power is affected by the study aim, the specificity of participant experiences, the guiding theoretical frameworks (COM-B [16, 61] and TDF [62]), anticipated data quality, and analytic strategy.

In the quantitative phase, we will administer a survey designed to understand providers’ capability, motivation and opportunities around lung donation and acceptance processes. Participants will occur via email invitation, with up to three reminders. Informed consent will be implied by survey completion after review of the study information sheet. After answering demographic questions and some broader questions about their donor management practices, participants will view a brief educational video introducing the LUNDON score. Participants will then answer questions about their interest in adopting the LUNDON score in their clinical practice. Survey instruments will be tailored for OPO representatives and lung transplant providers, respectively.

In the qualitative phase, we will conduct 45-minute semi-structured interviews with a purposive sample of survey respondents across high-, middle-, and low-performing OPOs and lung transplant centers based on publicly reported lung utilization and offer acceptance rates. Participants will provide written electronic consent before their interview. Interview guides, informed by the COM-B and the TDF frameworks, will be tailored to OPO and lung transplant provider roles and focus on behavioral drivers, contextual barriers and facilitators, and the perceived feasibility of LUNDON score adoption. Interviews will be conducted virtually via Zoom™, audio-recorded, transcribed verbatim, and thematically analyzed using NVivo™. Findings will be triangulated with survey results through a mixed-methods matrix to identify high-priority, modifiable implementation strategies aiming to support the development of resources in Aim 4.

### Aims 2 and 3: Assess the impact of the LUNDON score availability on clinical decision making related to donor management [among OPO representatives] and organ offer acceptance [among lung transplant providers]

We will recruit OPO personnel (Aim 2, N = 60) and lung transplant providers (Aim 3, N = 60) to participate in a simulation-based experiment designed to evaluate how access to the LUNDON score influences clinical decision-making. Purposive sampling will ensure representation from low-, medium-, and high-performing OPOs and lung transplant centers. Participants will be recruited via email invitation, with up to three reminders. Informed consent will be implied by initiation of the simulation activity and subsequent survey completion following review of the study information sheet.

Simulation activities will be conducted in SimUNet, a web-based platform developed by the United Network for Organ Sharing (UNOS) [63] that mimics real-time clinical workflows in DonorNet, the official system used by the Organ Procurement and Transplantation Network (OPTN) for management of donor information and organ offers. UNOS developed and maintains DonorNet as the OPTN contractor and created SimUNet for research and experimental purposes. SimUNet has been validated in national studies assessing kidney offer decisions, demonstrating both feasibility and realism for simulating transplant workflows [64,65].

After orientation to SimUNet, participants will view a brief educational video introducing the LUNDON score and its potential applications for lung donation and then complete 16 simulated case scenarios representing a range of donor risk profiles and clinical complexity. The order of scenario presentation and the visibility of the LUNDON score will be randomized to reduce order effects and individual bias. For each case, OPO personnel will provide donor management recommendations, while lung transplant providers will accept or decline organ offers; all participants will rate their decisional confidence and provide open-text justifications.

Quantitative data will be analyzed using generalized estimating equations to model within-subject differences in decision-making between scenarios with and without the LUNDON score. Prespecified subgroup analyses will assess heterogeneity by transplant center volume and by Lung Composite Allocation Score (CAS), a metric used by OPTN to assess transplant center performance based on waitlist, transplant, and post-transplant outcomes [12].

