### Lung donor (LUNDON) acceptability score

To address the need for more standardized, evidence-based tools for lung donor evaluation, our group previously developed and validated the Lung Donor (LUNDON) Acceptability Score [33], a predictive model that estimates the likelihood of donor lung utilization based on nine clinically relevant variables (**Table 1**) and correlates with post-transplant recipient outcomes [34]. Using a large national cohort from the Scientific Registry of Transplant Recipients (SRTR), we derived and validated the model in over 80,000 brain-dead donors. The LUNDON score demonstrates excellent discrimination and calibration across diverse donor populations [36,37]. The score is operationalized as a user-friendly, web-based tool (https://sites.wustl.edu/lundon/) that provides real-time case-specific probability estimates and supports more objective and reproducible decision-making in donor evaluation and management.

**Table 1 pone.0342383.t001:** LUNDON score component variables.

NON-MODIFIABLE VARIABLES	POTENTIALLY MODIFIABLE VARIABLES *(with possible donor management strategies for improvement)*
**• Donor age in years** **• Smoking history >20 pack-years (yes/no/unsure)** **• History of myocardial infarction (yes/no/unsure)** **• Mechanism of death by asphyxiation or drowning (yes/no)** • **Cardiac arrest after brain death (yes/no)**	**• PaO2/FiO2 ratio** *Lung protective ventilation*^15^ *Lung recruitment maneuvers*^15^ *Prone positioning*^37^ *Bronchoscopy*^15^ **• Abnormal chest x-ray appearance (yes/no)** *Frequent bronchoscopy* *Lung recruitment maneuvers* **• Maximum creatinine (mg/dL)** *Goal-directed fluid resuscitation*^38^ *Avoidance of nephrotoxic medications* *Renal replacement when indicated*^39^ *Hemodynamic optimization*^38^ **• Bloodstream infection (yes/no)** Prevention: *Isolation precautions, hand hygiene, sterile protocol for central line management* [40] Treatment: *Antibiotics, identification and drainage of infection source when indicated*

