## Methods/Design

*Aims:*

**Aim 1**: Identify determinants (barriers and facilitators) of LUNDON score adoption.**Aim 2**: Evaluate the LUNDON score’s impact on donor management at OPOs.**Aim 3**: Evaluate the LUNDON score’s impact on donor lung acceptance decisions at lung transplant centers.**Aim 4**: Develop and pilot implementation toolkits to support national dissemination and uptake of the LUNDON score.

*Timeline:* The complete study timeline is provided in Fig 1. At the time of manuscript submission, participant recruitment has not yet been completed for any study aim, and no study results have been generated. Recruitment and data collection will proceed in staged phases as outlined in the study timeline (Fig 1). At the time of protocol submission, no study results were available.

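### The educational video comes before every LUNDON item described in Aim 1 and before all 16 scenarios in Aims 2 and 3, so Aim 1 describes no baseline measure of awareness and Aims 2 and 3 estimate only the effect of displaying the score to people already taught about it

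*Protocol article*

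**What the plan says.** **Aim 1 survey.** The Aim 1 section gives the order: "After answering demographic questions and some broader questions about their donor management practices, participants will view a brief educational video introducing the LUNDON score". It continues: "Participants will then answer questions about their interest in adopting the LUNDON score in their clinical practice". Interviewees are then drawn from the survey respondents. The section on implementation frameworks counts knowledge as part of capability, one of the three COM-B components on which the survey is built.

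**Aims 2 and 3 simulation.** After orientation to the platform, "participants will view a brief educational video introducing the LUNDON score and its potential applications for lung donation and then complete 16" simulated scenarios. On randomization the article says: "The order of scenario presentation and the visibility of the LUNDON score will be randomized to reduce order effects and individual bias". The experiment is "designed to evaluate how access to the LUNDON score influences clinical decision-making", and generalized estimating equations will "model within-subject differences in decision-making between scenarios with and without the LUNDON score". The Aims list is broader; Aim 2, for example, reads "Evaluate the LUNDON score’s impact on donor management at OPOs".

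**Access outside the simulation.** The Introduction says of the score: "The score is operationalized as a user-friendly, web-based tool", and gives a public web address.

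**The concern.** In Aim 1, a participant who had never heard of the score has been taught about it before reaching the first LUNDON question that the article describes. Unawareness is an obvious candidate barrier, since the Introduction says the score is underused in routine practice. Whether the Aim 4 toolkits need the brief training modules listed as a possible component depends on how much users knew beforehand. That baseline is altered once the video has been shown, and the interviewees come from the same exposed group.

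In Aims 2 and 3, the hidden condition is an educated participant without the number on screen. Aim 2 is the more exposed, because its outcome is donor management and the frameworks section directs it at decisions on the modifiable score variables. If the video conveys which variables matter, a coordinator can act on them without seeing a score, and that part of the benefit falls in both conditions. A small contrast could then be reported as the score having little impact, and carried into Aim 4.

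**Working it through.** The plan gives no effect size, error rate, power or within-person correlation for Aims 2 and 3, so there is no figure to reproduce. The check sets the order of procedures against the stated aims.

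**Step 1: Aim 1 order.**

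| Stage | Content described | LUNDON measure described? |
|---|---|---|
| Before video | Demographics; broader practice questions | None |
| Video | Introduction to the score | – |
| After video | Interest in adoption | Yes |
| Interviews | Barriers, facilitators, feasibility | Yes, among people who have seen the video |

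The first LUNDON measure described comes after exposure.

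**Step 2: what the Aims 2 and 3 contrast identifies.** Let A be the decision with no video and no score, B with the video and the score hidden, and C with the video and the score shown. Introducing the score against current practice is

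C − A = (B − A) + (C − B).

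Everyone sees the video before case 1, so A is never observed. The model estimates C − B. The education term B − A is outside the data.

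Write f for the share of the full effect due to the video alone: f = (B − A)/(C − A). Then C − B = (1 − f)(C − A). The documents give no value of f, so these are assumed:

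| Assumed f | Contrast as a fraction of the full effect |
|---|---|
| −0.25 | 1 + 0.25 = 1.25 |
| 0 | 1.00 |
| 0.10 | 1 − 0.10 = 0.90 |
| 0.25 | 1 − 0.25 = 0.75 |
| 0.50 | 1 − 0.50 = 0.50 |

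The contrast equals the full effect only if f = 0. The table shows the gap between two questions; it is not an error in the estimate of C − B.

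**Step 3: carry-over.** Visibility varies within person, so a hidden case can follow cases where the score was seen. The article does not say how many of the 16 cases are shown, or whether visibility is randomized by case or in blocks. Assume 8 shown and 8 hidden in fully random order. Each shown case precedes a given hidden case with probability 1/2, so the expected number of scores already seen is 8 × 1/2 = 4. The chance that none has been seen is 1/(8 + 1) = 1/9, about 11%. Most hidden cases would then be open to carry-over. Random order spreads it over cases but does not remove it. How much it changes decisions is unknown. So is its direction: learning from earlier scores would narrow the contrast, while lower confidence when a familiar number is withheld would widen it.

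**The case against.** The strongest defence is that the Aims 2 and 3 design answers the question it states. The section heading speaks of availability, the text of access, and the frameworks section of how knowing a particular donor's score influences acceptance. Giving everyone the same video holds education constant, isolates display, and avoids showing people a number they may not be able to interpret. The article never says that the hidden condition represents current practice. All of this stands; only the broader wording in the Aims list goes further.

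A reader might infer that the contrast is biased toward zero and that power is lost. The documents do not support this: they contain no effect size, standard error or leakage fraction, and the direction is open. A reader might also want some hidden cases placed before the video. Those cases would always come first, always be hidden and always precede education. Video, position and visibility would be confounded, and the randomized order would be lost.

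On Aim 1, a reader might infer that lack of knowledge can no longer be detected as a barrier. That goes too far. The instrument is not shown, the pre-video practice questions could include an awareness item, and interviews can ask about prior awareness in retrospect. Asking about interest after explaining the tool is sensible. What remains is that no pre-video measure is described, and that recall after teaching is a poor substitute for one.

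**Conclusion.** The point holds in two limited parts. In Aim 1, the described order places the video before the LUNDON questions, with no earlier measure of awareness, use or knowledge, although knowledge belongs to a determinant the aim is meant to identify. In Aims 2 and 3, the contrast is valid for displaying the score to educated users. It does not support a conclusion about the score's overall impact against current practice.

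No numerical size can be given. The fractions in the working rest on an assumed f, and the carry-over counts on an assumed 8/8 split in fully random order. The Aim 1 part rests on the survey order as described and falls away if the full instrument already has such items before the video. The importance is moderate: nothing invalidates the experiment, but baseline awareness cannot be recovered cleanly after the video.

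**What to change.** **Aim 1.** Add two or three items before the video on awareness, current use and knowledge of the score. Keep the interest items after it. The cost is a slightly longer survey. Recruitment was expected to begin on 01/02/2026 and run through 30/06/2027; if the survey is already open, the items can serve only the remaining respondents.

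**Aims 2 and 3.**
- Keep the video first and the randomized order as planned.
- State the conclusion as the effect of displaying the score to educated users, and align the wording of Aims 2 and 3 with it.
- Add case position and number of scores already seen to the model as a carry-over sensitivity analysis. This needs a log of the order and visibility of each participant's cases. It is most informative if visibility is randomized by case, because in blocks the number seen is tied closely to visibility.
- Tell participants not to use the public web calculator during the simulation, and ask afterwards whether they did.

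The cost is a wording change, one secondary model, one instruction and one question, with no extra participants or scenarios. Recruitment for these aims is not expected before 01/03/2027.

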#### Aim 4: Develop and pilot-test implementation toolkits for LUNDON score adoption.

Based on the findings from Aims 1–3, we will follow a structured process [66] to develop a set of participant-informed implementation toolkits to support real-world use of the LUNDON score. This will proceed in three phases:

• Phase 1: Develop an Implementation Research Logic Model (IRLM), to graphically depict relationships among study elements, aid future study replicability, and evaluate the implementation process [67]. A proposed IRLM for this study is provided in **Fig 2**. In Aim 4, the IRLM will be revised to incorporate findings from Aims 1–3, using the COM-B model and the TDF to systematically map identified behavioral determinants of LUNDON score adoption. The research team will then link these determinants to corresponding implementation strategies and potential toolkit resources.

**Fig 2 pone.0342383.g002:**
[figure not shown]
Proposed implementation research logic model that will be adapted to incorporate findings from Aims 1-3.

Phase 2: Develop tailored toolkits for OPOs and lung transplant centers, comprised of resources to address the site-specific contextual needs for LUNDON score implementation. Guided by COM-B and TDF, toolkit development will draw on findings from Aims 1–3, clinical experience, and the input of multiple key constituent groups. Toolkit components may include decision-support aids, brief user training modules, electronic health record integration templates, and/or communication scripts tailored to clinical workflows.Phase 3: Refine toolkits through a brainwriting [68] pre-mortem exercise [69], which is a proactive planning method that uses prospective hindsight to anticipate potential reasons for implementation failure and generate solutions before the intervention is deployed. Focus groups will engage key constituents (n = 48) to assess content, format, acceptability, and usability, and will proactively identify weaknesses, barriers to adoption, and potential points of failure in the toolkit design. Participants will be offered a $125 Visa gift card as compensation.Phase 4: Pilot test the toolkits at three OPOs and three lung transplant centers. Pilot testing will include brief user testing followed by structured interviews with decision-making personnel at each site (n = 12) to assess acceptability, feasibility, and suggestions for improvement. Qualitative data will inform iterative refinement of materials. Interview participants will be offered a $125 Visa gift card as compensation.

### Safety considerations

This is a minimal-risk study. The primary potential risks is a breach of confidentiality, which will be mitigated through use of secure data platforms and IRB-approved data protection procedures. No biomedical interventions or physical risks are associated with participation.

### Data management

All study data will be managed using secure, access-controlled platforms in compliance with institutional policies and relevant federal regulations. Each participant will be assigned a unique study ID, and all personally identifiable information will be stored separately from analytic datasets. Data access will be restricted to approved study team members.

Survey data (Aims 1–3) will be collected and stored in REDCap. Interview recordings will be transcribed verbatim by a secure transcription service and uploaded to NVivo for qualitative coding and thematic analysis.

Routine data quality checks will be conducted weekly to identify missing or inconsistent entries. Periodic data backups will be stored on encrypted institutional servers. Final analytic datasets will be de-identified, with documentation maintained for transparency and reproducibility. Following study completion, data will be made available to qualified researchers upon request and IRB approval.

### Ethics approval and consent to participate

This study protocol has been reviewed and approved by the Institutional Review Boards (IRBs) of Washington University [IRB # 202504071] and Duke University [IRB # Pro00118530]. All participants will provide informed consent prior to participation.

### Dissemination plan

Study findings will be disseminated through peer-review publications, including this protocol and subsequent results manuscripts. Results will also be presented at national conferences focused on transplantation and implementation science. Upon study completion, finalized implementation toolkits will be made freely available through an open-access study website and shared with the broader transplant community via UNOS and professional society networks to support real-world application.

## Discussion

Despite substantial progress in donor management and organ allocation, lung utilization in the United States remains low, with wide variation across centers and persistent gaps between evidence and practice. The LUNDON score offers a validated, data-driven approach to predict donor lung utilization and post-transplant outcomes; however, its integration into routine donor management and clinical decision-making has been limited. This study addresses a critical gap in the literature by applying implementation science methods to identify behavioral, organizational, and contextual determinants of LUNDON score adoption and by developing actionable, theory-informed strategies to promote its routine use.

This work represents a collaborative, nationally supported effort involving partners from the United Network for Organ Sharing (UNOS), the surgical and medical lung transplant community, and OPOs. The study rationale, design, and proposed interventions have been shaped by direct input from these constituent groups, ensuring alignment with clinical practice realities and system-level priorities. By systematically identifying barriers and facilitators and translating these findings into practical implementation tools, this study aims to bridge the evidence-to-practice gap and improve donor lung utilization nationwide.
